## Methods

6.

This project has received ethical clearances and research approvals from the Children’s Health Queensland Human Research Ethics Committee (HREC/20/QCHQ/70612), the University of Queensland (2021/HE001359), and Department of Youth Justice and Multicultural Affairs.

### Stakeholder consultation and co-design

6.1.

Phase one will involve stakeholder consultation that will contribute to the co-design of an IMHIP-Youth model. Structured consultations with stakeholders will seek to answer several of the Phase one research questions, pertaining to the landscape domain.

Consultation and co-design with community is a commitment to establishing and using shared language, openness of information and addressing power imbalances with all experts throughout the process. The opportunity is co-design through multiple perspectives with differing views acknowledged and accepted with all working in partnership to develop, prioritize, implement and evaluate outcomes. Those involved throughout all stages are acknowledged and provided with opportunities to opt in and out of the process. The project team’s role is to listen, assess and integrate the information shared in a transparent way. In this way, consultation within a co-design framework differs from earlier models of community consultation in that it will go beyond simply obtaining information to analyze and inform decision making, within pre-specified parameters, to instead ensure that concerns and aspirations are consistently understood and considered. Co-design will be a meaningful and authentic process, that shares power and builds partnerships to co-create health services.

Co-design and consultation will be undertaken with relevant stakeholders, including:

Aboriginal and Torres Strait Islander young people who have experienced detentionAboriginal and Torres Strait Islander EldersFamilies and carers of Aboriginal and/or Torres Strait Islander young people who experience detentionRelevant Government DepartmentsIMHIP staffNon-Government Organization providers who work with justice involved young peopleStaff who deliver health services within youth detention centers and once in community.

### Co-design with adult stakeholders (adults, 18 years and over)

6.2.

Focus groups, meetings, panel discussions, and one-on-one consultations will occur with Elders and other stakeholders, in order to understand elements of the *Landscape domain* through understanding needs, mapping historical and contemporary contextual factors, mapping the current services context, and envisioning what success would look like. This will ensure that a comprehensive understanding of stakeholder perspectives is gathered. It is envisaged that 6–12 individuals will participate per stakeholder group to gather diverse views. A multi-stakeholder workshop will also be held to summarize findings of the consultation and develop consensus around the model of service to be implemented and finalize details of its evaluation. This is a critical step to informing service design. Specific stakeholder views (i.e., excerpts of narratives or transcribed audio) will not be published as a research output.

All stakeholders who are engaged will be supplied with information sheets describing the nature of the study and their participation or directed to the project website, www.IMHIP-Youth.org, which will be regularly updated and provides a comprehensive repository of information on the project. Verbal consent to participate will be sought, but participants will not be asked for signed written consent forms, due to the fact that the primary purpose of this engagement is consultation and data gathering with respect to services and systems but is not to collect the opinions or attitudes of individuals themselves for the purposes of research on individuals. Collecting written consent forms would be out of keeping with norms of co-design and consultation processes and could restrict or skew the engagement process and/or flow of ideas.

### Engagement and co-design with Aboriginal and Torres Strait Islander young people (<18) who have experience of detention

6.3.

Processes for recruiting and gathering consent from young Aboriginal and Torres Strait Islander peoples are described below.

#### Eligibility

6.3.1.

Aboriginal and Torres Strait Islander young people will be eligible to participate in Phase one of this study, if they:

Identify as an Aboriginal and/or Torres Strait Islander personWere or are aged 10–17 years old at the time of their offence date for which they entered into detention, during the recruitment periodEntered one of the two Brisbane youth detention centers during the recruitment period, or left detention in the 12 months priorFor those in detention only, have been received into detention within the past 7 days OR are already in detention, but not received in the past 7 days, in which case they are eligible to participate in an initial interview, but will not be followed up, andHave sufficient understanding, intelligence and maturity to appreciate the nature, consequences and risks of consenting to participate in the study and the alternatives, including the consequences of not consenting to participant.

#### Consent

6.3.2.

Prior to commencing recruitment, all staff from the above-mentioned services and organizations who will be assisting in recruitment will receive a project orientation, through an introductory presentation by project team members. This will include an overview of the aims of the project, discussion of informed consent processes, and training to ensure that appropriate cultural protocols are followed in recruiting and engaging young people and their parents. The engagement with parents and care-givers is an important part of the consent process as consent by young people is complex due to a number of factors including age, developmental stage, capacity, language and comprehension to what they are providing consent for. To safeguard the young person’s and family rights, and to honor co-design, parents and care-givers will be provided with the same level of information and opportunity to ask questions to ensure informed consent is given throughout the process. Where possible, individuals involved in recruitment of participants will be Aboriginal and/or Torres Strait Islander people.

When determining a young person’s capacity to provide free and informed consent to participate, researchers will be guided by Queensland Health Guidelines on the assessment of a child’s capacity to provide consent, which include consideration of the following:

the age, attitude and maturity of the child or young person, including their physical and emotional developmentthe child or young person’s level of intelligence and educationthe child or young person’s social circumstances and social historythe nature of any condition the child or young person may be diagnosed witha young person aged between 16 and 18 is most likely able to consenta young person aged between 14 and 16 is reasonably likely to be able to consenta child under the age of 14 may not have the capacity to consent

All eligible participants will be approached during the period of recruitment for Phase one (planned for 8 months, beginning in July 2021), or until 110 individuals are consented. Participants and their parents or guardians will be asked to provide consent for:

primary qualitative and quantitative data collection (described in data collection section, below)consent to be contacted by researchers in the future to undertake further data collection relating to the project’s evaluation, andconsent for the operating department of the youth detention centers to provide identifying details, including aliases, to an independent government statistical organization to undertake data linkage, that will occur during Phase 2 of the research. Data linkage will be to health, education custodial datasets.

#### Recruitment

6.3.3.

For Phase one, Aboriginal and Torres Strait Islander young people who have experienced detention will be recruited through:

Forensic Child and Youth Mental Health Service in detention and communityBrisbane Youth Detention Centre or West Moreton Youth Detention CentreParticipating community-controlled organizations

##### Recruitment via forensic CYMHS

6.3.3.1.

The recruitment and consent process via the existing Forensic Child and Youth Mental Health Services is given in Figure 2. Individuals meeting study eligibility criteria will be engaged by clinicians who have received orientation and training, to explain the project to the prospective participant in written and spoken form. The young person will asked if they would be interested in being contacted by a researcher to obtain consent from them and their guardians to participate. The young person will be informed that they can withdraw this consent at any time.

**Figure 2 fig2:**
[figure not shown]
Recruitment and consent process via Forensic CYMHS.

If an individual gives consent for a project researcher to seek parent or guardian consent, Forensic CYMHS will contact the project researcher to provide contact details for the young person’s parent or guardian. If the participant is in custody, the in-custody guardian will be contacted to advise them of the participant’s interest and to plan to meet with both parties to explain the study. When the young person and in-custody guardian have consented, researchers and the in-custody guardian will contact the relevant community parent/guardian, to obtain verbal consent for participation. If the community parent/guardian does not consent, then the interview will not proceed. If the community parent/guardian cannot be readily contacted (i.e., two unsuccessful attempts are made over a 24 h period), the interview will proceed on the basis of the consents obtained. The researcher will contact the community parent or guardian to obtain written consent if the young person is not in custody at the time of approach.

##### Recruitment via youth justice pathways, within Brisbane Youth Detention Centre and West Moreton Detention Centre

6.3.3.2.

The recruitment and consent processes within the detention centers will follow a similar process to recruitment via Forensic CYMHS. This recruitment process is provided in Figure 3. Individuals meeting study eligibility criteria will be engaged by a delegated staff member working in the centers who has received orientation and training, to explain the project to the participant in written and spoken form. The young person will asked if they would be interested in being contacted by a researcher to obtain consent from them and their guardians to participate. The young person will be informed that they can withdraw this consent at any time.

**Figure 3 fig3:**
[figure not shown]
Recruitment via Brisbane Youth Detention Centre and West Moreton Detention Centre pathways.

If an individual gives consent to be contacted and for a researcher to seek guardian consent, the delegate will contact the project researcher to provide contact details for the young person’s guardian. If the participant is in custody, the in-custody guardian will be contacted to advise them of the participant’s interest. When the young person and in-custody guardian have consented, researchers and the in-custody guardian will contact the relevant community parent/guardian, to obtain verbal consent for participation. If the community parent/guardian does not consent, the interview will not proceed. If the community parent/guardian cannot be readily contacted (i.e., two attempts are made over a 24 h period), the interview can proceed. The researcher will contact the community parent or guardian to obtain written consent if the young person is not in custody at the time of approach.

##### Recruitment via Aboriginal and Torres Strait Islander community controlled organizations

6.3.3.3.

In addition to recruitment within detention settings, some recruitment will occur among individuals who are in the community (Figure 4). This will be critical to informing the design of the transitional service, by engaging and hearing the perspectives of individuals who have left detention and are in the community. Recruitment via Aboriginal and Torres Strait Islander Community Controlled Organizations will occur via online channels (e.g., mass emails or newsletters). Project information, an invitation to participate in the research, information regarding the nature of the project and participation information will be provided at this time.

**Figure 4 fig4:**
[figure not shown]
Recruitment and consent via community controlled organizations.

Individuals who contact the project team via this channel will be followed up as soon as is practicable by a member of the research team. The researcher will explain the study to the young person and their parent or guardian, and seek their consent. The process of seeking consent could occur simultaneously, if parents and children agree and are available at the same time; otherwise it will occur sequentially. A CYFMHS clinician will join the project team member for the purposes of assessing that the prospective participant has capacity to consent. However, it should be noted that we anticipate that many individuals recruited via this pathway will be 18 or 19 years of age at the time of interview, and therefore parent or guardian consent will not be required.

#### Request for additional de-identified linked data for young people who experience detention, where a waiver of consent will be sought

6.3.4.

The unforeseen events of the COVID-19 pandemic have had several impacts on young people in detention. It is unknown what impacts these will have on trends in social and emotional wellbeing, or educational, vocational or criminal justice outcomes. In order to improve the evaluation in the context of unknown COVID-19 related variation, we are requesting linked data for two historical cohorts, based on entrants into youth detention for two 8 months periods in the 2 years prior to the recruitment phase of the project. It is not feasible to contact or obtain consent from these individuals, and therefore a waiver of consent is requested for these cohorts.

### Data collection

6.4.

#### Aboriginal and Torres Strait Islander young people with experience of detention

6.4.1.

The target sample size for Phase one recruitment is 110 individuals, comprising 80 individuals who are received into detention within the last 7 days, during the recruitment period, and 30 individuals who are in the community, but had an experience of youth detention in the 12 months prior or who are in detention, but have been in detention for more than 7 days during the period of data collection. Individuals will be recruited over an approximate 8-month period commencing in July, 2021.

All young people who agree to participate in Phase one of this research will be invited to participate in an initial interview. The 80 individuals who are recruited within 7 days of detention will also be invited to participate in a series of follow-up interviews that will provide baseline data for quantitative comparison. Planned follow up interviews will take place at 30 days following the initial interview, 6 months following the initial interview and 12 months following the interview. Interview schedules are described below.

#### Initial interview

6.4.2.

Interviews will take place at a time that does not conflict with structured programs that the young person should be engaging with in detention. The initial interview will be a one-on-one interview with an experienced Aboriginal and/or Torres Strait Islander interviewer, trained additionally for IMHIP-Youth. Interviews are a supportive respectful way to hear young people’s perspectives. They have also been chosen as a data collection method due to identified limitations to open disclosure among young people in detention in group-based settings as well as because of the detail required about topics in relation to which data are gathered. Culturally-safe, age-relevant questions, including life journey drawing and scenarios, will be used to engage with young people within the context of, what Bessarab and Ng’andu (34) have described as, “research topic yarning.” Yarning describes an Aboriginal form of communication and conversation for building respectful relationships within a culturally safe space. The ‘yarn’ forms the basis for relational interactions, knowledge and information sharing, giving or finding for a collective and collaborative understanding. Importantly, yarning refers to the establishment of a relationship with participants prior to gathering stories. Interviews will seek to understand young people’s needs and priorities in the context of their narratives of past, present, and future (34).

Interview will take approximately 45 min, to ensure that young people do not experience undue fatigue. Young people will be able to cease the interview at any time and for any reason, and they will have the option to recommence and complete the interview over two sessions, if they wish. They are also able to withdraw consent to participate at any time, by notifying the researcher they are engaging with or contacting a project team member (contact details will be provided on information sheets).

##### Measures and interview guide

6.4.2.1.

The interview will begin with the Growth and Empowerment Measure (GEM) (26). The GEM was developed by and validated for Aboriginal and Torres Strait Islander Australian adults, however, it has been successfully used among young people. The GEM is a 26-item self-report measure using culturally-relevant scenarios and language to understand social and emotional wellbeing, connections with others and empowerment. The GEM has been modified for this study, modifications include: simplification of language, and modification of questions to reflect the age of participants (e.g., reference to having children will be removed from response formats, and references to employment and training will be reworded to incorporate participate in schooling). The GEM-Youth, will be piloted and validated at the beginning of the project. The GEM-Youth instrument (as well as the K-10) will be completed on paper or tablet, with the trained interviewer actively participating in the young person’s completion of these instruments, to ensure that questions are understandable and understood by participants, including those who may have literacy issues, and that answers given are an accurate reflection of the young person’s views or attitudes.

After the GEM the interviewer will administer the Kessler-10. K-10 is a widely used measure of 30-day psychological distress, with well-established validity and reliability. The K-10 has been culturally validated with Aboriginal and Torres Strait Islander people.

Additionally, identifying data and socio-demographic data will be recorded on:

Name, including any aliasesDate of BirthCurrent AddressChild Protection Status (No Child Protection Order, Historical CPO, Intervention with Parental Agreement, Temporary Custodial Child Protection Order, Long Term Guardianship Child Protection Order)Sex/Gender (Male, Female, Other)

The interview will end with supportive reflection on the young people’s story through a narrative interview that will explore topics such as:

What led them to being in detention – the factors, not crimeWhat their experience of detention is (or was) like, what programs they participate(d) in, what they are hoping to achieveHow they feel about their health and wellbeing, including social and emotional wellbeing, and any mental health concernsWhat they hope to do when they leave detention (or what they have done since leaving detention), what concerns they might have for their future, and longer-term aspirations they may have including for education and vocation.What they would like from a service that was designed to help improve their social and emotional wellbeing, and what success would look like to them.

Six alcohol and drug questions will also be asked, as follows:

Do you drink alcohol? (Yes/No)If Yes■ are you worried or concerned about your drinking? (Yes/No)■ have your family or friends said that they are worried or concerned about your drinking (Yes/No)Do you use drugs? (Yes/No)If Yes■ Are you worried or concerns about your drug use? (Yes/No)■ Have your family or friends said that they are worried or concerned about your drug use? (Yes/No)

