#### Interviews at 30 days, 6 and 12 months following reception into detention

6.4.3.

Young people (*N* = 80, target) who are recruited in detention will be asked if they consent to be followed up at 30 days following the interview, and again at 6 months and 12 months following the interview.

The interview that takes place at 30 days, 6 months and 12 months will be a brief ‘check-in’, principally for the purposes of gathering GEM and K-10 measures, as well as alcohol and drug questions.

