#### Quantitative analysis

6.5.1.

Quantitative data collected from Phase one will be analyzed using descriptive statistics to provide a profile of the cohort. Inferential statistics (ANOVA, Chi-squared tests, linear regression) will be used to compare sociodemographic factors and measures of mental health, and social and emotional wellbeing, and educational and criminal justice outcomes, across the three recruitment channels. Associations between sociodemographic factors and mental health and wellbeing will also be explored. Latent class analysis and/or group-based trajectory modeling will be used to analyze the trajectory of outcomes over time and to explore whether there are meaningful subgroups within the population.

GEM-Youth and K-10, along with alcohol and drug questions, collected from young people in detention (i.e., recruitment via child and youth mental health service and the Aboriginal and Torres Strait Islander unit), as well as socio-demographic data, will be used as comparison with the intervention cohort in Phase 2. Identifying data (Name, Date of Birth, Address) will be used for the purposes of data linkage.

The GEM-Youth will be piloted during the first five interviews of this study. Any issues identified with language, understanding or logistics of this tool will be discussed among investigators [name], [name], [name] and [name], and a decision will be made as to whether modifications to the tool are required. Following completion of initial interviews, the GEM-Youth will be validated, against the K-10. The methodology will follow the approach taken by Haswell et al. (26), in their Psychometric validation of the GEM. The psychometric properties and internal structure of the GEM (Adult) was examined against the K6 and K6 + 2, utilizing Pearson’s correlations, Cronbach’s alpha, and Principal Components Analysis.

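### The alcohol and drug stem items have no reference period, so change over time and cohort differences on them can be confounded with custody status

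*Protocol article*

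**What the plan says.** Section 6.4.2.1 (Measures and interview guide) introduces the items with "Six alcohol and drug questions will also be asked, as follows" and then prints them with their response options. The stems are "Do you drink alcohol" and "Do you use drugs? (Yes/No"; neither carries a time window. Four further items, on the young person's own worry and on worry voiced by family or friends, follow only after a Yes. In the same section the companion scale does have a window: "K-10 is a widely used measure of 30-day psychological distress".

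Section 6.4.1 sets a Phase one target of 110. Of these, 80 are recruited within 7 days of reception into detention and followed up. The other 30 are either in the community after detention in the past 12 months or have been in detention for more than 7 days.

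Section 6.4.3 describes the 30-day, 6-month and 12-month contacts as "principally for the purposes of gathering GEM and K-10 measures, as well as alcohol and drug questions". Section 6.5.1 lists, among the data to be compared with the Phase 2 intervention cohort, GEM-Youth and K-10 "along with alcohol and drug questions, collected from young people in detention".

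Two other statements bear on setting. Section 2.2.1 describes time in detention as often brief, and section 4.2 makes less criminal justice contact and less reincarceration a Phase 2 question.

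**The concern.** A question about drinking or drug use with no window can be taken in two ways. A young person in detention may answer No because there is no use at present, or Yes because use is usual outside. In the community the two readings mostly agree; in custody they can part. The same habit can then give different answers in different settings.

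Every member of the followed cohort is in detention at the first interview. Because detention is often brief, later interviews will probably fall in mixed settings. That is an inference: the article does not state the setting of each follow-up. Change from the first interview is therefore exposed. So is the Phase 2 comparison, if the share in custody at follow-up differs between cohorts, and the program is meant to lower that share. If it does, more of the intervention cohort would be answering from the community, and more might say Yes with no difference in habit.

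The worry items share the problem, because the stem decides who is asked them. Section 6.5.1 also plans comparisons across recruitment channels, one of them community-based, and trajectory modelling of outcomes. If these items enter those analyses, they are exposed there too.

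**Working it through.** **The plan's own figure.** 80 followed + 30 interviewed once = 110, as section 6.4.1 states. The article gives no prevalence of use, no custody share at follow-up and no power calculation, so the rest is an illustration on assumed inputs.

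**Model.** Let
- u = share who usually use when in the community, held constant so that there is no true change in habit (assumed 0.5 or 0.8);
- m = share of users in custody who answer No because they read the stem as asking about now (assumed 0, 0.25, 0.5 or 1);
- c = share in custody at the interview.

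Then P(Yes) = u × (1 − m × c).

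*Change within the cohort.* At the first interview c = 1. If c falls to c₁₂ at 12 months, the change is u × m × (1 − c₁₂). With u = 0.5, m = 0.5 and c₁₂ = 0.5: 0.5 × 0.5 × 0.5 = 0.125, or 12.5 points.

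*Difference between cohorts.* With custody shares c₀ (comparator) and c₁ (intervention), the difference is u × m × (c₀ − c₁). With u = 0.5, m = 0.5, c₀ = 0.5 and c₁ = 0.3: 0.5 × 0.5 × 0.2 = 0.05, or 5 points more Yes in the intervention cohort.

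*False rejection.* Two-sided 5% normal test of that difference, assuming 80 per cohort and no loss to follow-up. For the same case, p₀ = 0.375 and p₁ = 0.425. SE = √(0.375 × 0.625/80 + 0.425 × 0.575/80) = 0.077, so z = 0.65 and the rejection rate is 9.9%.

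| u | m | Within, c 1.0 → 0.5 | Within, c 1.0 → 0.2 | Between, c 0.5 v 0.3 | False rejection (between) |
|---|---|---|---|---|---|
| 0.5 | 0 | 0 | 0 | 0 | 5.0% |
| 0.5 | 0.25 | 6.25 | 10 | 2.5 | 6.2% |
| 0.5 | 0.5 | 12.5 | 20 | 5 | 9.9% |
| 0.5 | 1 | 25 | 40 | 10 | 28.4% |
| 0.8 | 0 | 0 | 0 | 0 | 5.0% |
| 0.8 | 0.25 | 10 | 16 | 4 | 8.7% |
| 0.8 | 0.5 | 20 | 32 | 8 | 18.5% |
| 0.8 | 1 | 40 | 64 | 16 | 53.7% |

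Differences are in percentage points.

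The between-cohort column is zero whenever c₀ = c₁, whatever m is. Every column is zero when m = 0, that is, when all respondents answer for usual behaviour. The table shows direction and sensitivity only; nothing in the article says which row applies.

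**The K-10 contrast.** A window by itself does not remove the dependence on setting. A plain 30-day window would define what is measured, but the answer would still depend on how many of those days were spent in custody. What removes the ambiguity is a window that refers to time in the community, together with knowledge of custody status.

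**The case against.** The strongest reply is that a simple-present question normally asks about habit, that the follow-on items about worry point the same way, and that a trained interviewer sits with the young person. If all respondents take it so, m is zero and custody has no effect. That stands as a possibility. The article does not say that interviewers are to steer respondents to that reading.

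A reader might infer that change on these items tracks custody in place of use, or that a successful program will look harmful. The documents do not support either statement. Both need a present-state reading by some detained respondents, and the second also needs a difference in custody mix at follow-up. Neither is shown.

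Four further points stand:
- Custody may truly restrict access, so a No from a detained respondent can be a correct report of current use. The items as printed cannot separate that from a different reading of the question.
- Substance use is not among the outcomes in the section 4.2 research question, and follow-up is mainly for GEM and K-10. These are secondary items.
- If Phase 2 recruits in the same way, both cohorts are in early detention at the first interview, so setting does not differ there.
- Sections 6.3.2 and 6.4.4 plan linkage to custodial data, which may supply custody status for those who consent. It cannot show which meaning a respondent used.

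The reply that wording belongs in a fuller document does not stand, because the article prints the six items in full.

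**Conclusion.** The point holds as a moderate one. The stems lack a reference period, are asked repeatedly of a cohort that starts in detention, and are named as Phase 2 comparison data. Change over time and cohort differences on them can therefore be confounded with custody status. If the program lowers reincarceration, the direction of the bias would be against it.

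The size is unknown. With 50% to 80% usual use and a 20-point lower custody share in the intervention cohort, the between-cohort artefact runs from 0 to 16 points as the share answering for the present runs from none to all. Within the cohort, with 50% or 20% still in custody at 12 months, it runs from 0 to 64 points. All these inputs are assumptions, and the figures are not evidence that bias will occur.

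**What to change.** 1. Give both stems a stated reference period that means the same in both settings. For example, at the initial interview use the 30 days before entering detention for those in custody and the last 30 days for those in the community. At follow-up use the most recent 30 days in the community, with a response option for not having been in the community since the last interview. A single pre-detention window for everyone would not suit those recruited in the community, whose detention may be up to 12 months past.
2. Use identical wording in Phase 2.
3. Record custody status at each interview, or take it from the linked custodial data for those who consent.
4. Report the items for all respondents and by custody status. Do not make the subset with community time the main comparison: time in the community is something the program aims to change, so restricting to it selects on a post-intervention state.

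The cost is the wording of two items, one response option and at most one status field. The downside is that recruitment was planned over about 8 months from July 2021. Any interviews already done with the current wording must be flagged and are not directly comparable with later ones on these items; flagging does not restore that comparison.
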